## Abstract

**Background:**

Chest tube insertion is a standard intervention for management of various injuries of the thorax. Quick and accurate execution facilitates efficient therapy without further complications. Here, we propose a new training concept comprised of e-learning elements as well as continuous rating using an objective structured assessment of technical skills (OSATS) tool. The study protocol is presented for a randomized trial to evaluate e-learning with app-based serious gaming for chest drain insertion.

**Methods:**

The proposed randomized trial will be carried out at the Department of Orthopedics and Traumatology at Heidelberg University in the context of regular curricular teaching for medical students (*n* = 90, 3rd to 6th year). The intervention group will use e-learning with the serious gaming app Touch Surgery (TM) for chest drain insertion, whereas the control group uses serious gaming for an unrelated procedure. Primary endpoint is operative performance of chest drain insertion in a porcine cadaveric model according to OSATS.

**Discussion:**

The randomized trial will help determine the value of e-learning with the serious gaming app Touch Surgery (TM) for chest drain insertion by using the OSATS score. The study will improve surgical training for trauma situations.

**Trial registration:**

Trial Registration Number, DRKS00009994. Registered on 27 May 2016.

**Electronic supplementary material:**

The online version of this article (doi:10.1186/s13063-017-1799-5) contains supplementary material, which is available to authorized users.

## Background

Chest tube insertion is an established minimally invasive surgical intervention in treatment of acute trauma patients bearing injuries of the lungs and thorax. It is the gold standard with regards to emergency care of pneumothorax or serial rib fractures as well as lesions of pulmonary vessels resulting in a hematothorax [1]. Chest tube insertion is equally performed in preclinical care and the clinical setting, yielding the need for procedural proficiency of physicians in both the field and the in-hospital emergency setting. Anatomical knowledge of the structures involved, an accurate positioning and standardized execution are crucial to a treatment, which is as quick and accurate as possible. Correct chest tube insertion facilitates efficient therapy without time loss or further complications that are potentially lethal because of the intervention’s vicinity to vital organs [2]. Thus, there is a need for a comprehensive training and assessment prior to the emergency situation that enables both versed physicians and novices to acquire proficiency in chest tube insertion. Early and decisive training using a tool as such might standardize handling of these emergency situations and could translate to improved trauma care and outcome. E-learning has been shown to be a valuable asset to surgical training [3–5]. Since computer games are believed to be commonplace for today’s students and their experience potentially enables them to profit from different approaches, the concept of ‘serious gaming’ is subject to training research [6–9]. Since serious games have already been evaluated in various situations within the framework of surgery, our aim is to expand the investigation of this multimedia training approach to trauma medicine and standard emergency interventions.

To advance and standardize training success without straining staff and resources, we use an objective structured assessment of technical skill (OSATS) for chest tube insertion to standardize expert rating [10]. The OSATS tool for chest drain insertion was developed based on key steps of correct chest tube insertion, originally published by Hutton et al., which were modified and amended by a team of trauma and general surgeons [11]. Ten representative procedural steps can be evaluated separately using a 5-point Likert scale complemented by detailed formulation of performance levels. Trainee’s performance in sub-steps adds up to a maximum total score of 50 points and a minimum score of 10 points, respectively.

The OSATS is used in a randomized controlled trial (RCT) investigating a serious gaming approach for training of chest tube insertion for medical students in a standardized and structured setting with the validated surgical training app Touch Surgery™ (TS) (Kinosis Ltd., London, UK) [12]. The study protocol for the RCT is described in the present manuscript.

## Methods and Design

### Objectives

Primary objective of this study is to evaluate training outcome of a structured chest drain training curriculum that comprises elements of serious gaming. Both operative and time-dependent performances of participants are analyzed. Secondary goals include character profiling concerning previous experience and specific extracurricular activities. Thus, participants particularly benefiting from the presented training concept as well as obstacles and positive impulses when training with standardized E-learning platforms might be identified. Evaluation of serious gaming elements in student teaching is also performed to evaluate the potential establishment of such modalities in medical school curricula.

### Study design

This is a registered prospective, single-center, rater-blinded, two-arm, parallel-group randomized controlled trial (DRKS00009994).

### Setting and participants

This study is carried out in the training center of the Department of Orthopedics and Traumatology at Heidelberg University. This study is conducted in the context of regular curricular teaching for medical students during their clinical years (3rd to 6th year) at Heidelberg University.

### Inclusion and exclusion criteria

The inclusion criterion mandates that participants are medical students in their clinical years (3rd–6th year) at Heidelberg University who have completed their 18th year of age. Previous participation in surgical training courses including insertion of chest drains is not an exclusion criterion but will be recorded and analyzed.

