### Assessment

Participants perform chest drain insertion on an accordingly prepared porcine model during the second training session. Performance is videotaped and rated by two different raters on-site using the modified OSATS tool for chest drain insertion (Table 1). The raters are blinded to the training status of the participants. An additional video-based evaluation is performed by a blinded rater according to the same scoring tool. The modified OSATS for chest drain insertion was evaluated in a pilot study and showed good construct validity for distinction between experience levels. Unblinding of raters or employees involved in data analysis and interpretation is not intended. To prevent selection bias, baseline characteristics including age, year of studies, previous experience, gender and hobbies will be compared. Baseline testing on a porcine model is not performed as the hypothesis is that the proposed curriculum, consisting of multimedia training material only, will directly improve performance. The aim of the training curriculum and study is to prepare novices for their first performance of chest drain placement. Baseline testing on a real model could disguise the effect of the training curriculum.

**Table 1 Tab1:** Objective structured assessment of the technical skills score for chest tube insertion

Correct identification of incision location	1 **Poor** The chosen dissection plane deviates tremendously from the suggested site	2	3 **Sufficient** The chosen dissection plane deviates slightly from the suggested site	4	5 **Excellent** 4th/5th intercostal space; mid/anterior axillary line
Correct plane of dissection subcutaneously	1 **Poor** Both distance or execution of tunneling lack accuracy	2	3 **Sufficient** Either distance or execution of tunneling lack accuracy	4	5 **Excellent** Both distance and execution of tunneling are accurate
Blunt dissection on top side of rib	1 **Poor** Flawed dissection; not carried out on top side of rib	2	3 **Sufficient** Solid dissection carried out with minor errors	4	5 **Excellent** Confident cut through the subcutaneous layers and intercostal muscles
Scissors/clamp guarded with other hand during dissection and pulled out without closing the instrument	1 **Poor** Hazardous handling that might affect the patient	2	3 **Sufficient** Improvable handling	4	5 **Excellent** Confident handling of the used instruments

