### Statistical analysis

Mean and standard deviation in case of continuous data, with absolute and relative frequencies for categorical parameters, are used to describe the distributions of all parameters of interest. Possible differences of the primary outcome and OSATS score will be tested using analysis of covariance with intervention group as factor, participants’ self-attributed expertise score as covariate and OSATS score after intervention as dependent variable. Secondary endpoints will be descriptively analyzed according to their respective distribution with t-tests in case of continuous data and chi-square test in case of categorical data. Multiple imputation will be applied to compensate for any missing data. If it is found to be appropriate, graphical statistical methods will be deployed to illustrate findings.

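### The primary ANCOVA adjusts only for a self-rated expertise score and omits recorded prior training, year of studies and the stratification factor, which forgoes precision but does not cause bias

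*Protocol article*

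**What the plan says.** All references are to the protocol article.

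- **Inclusion and exclusion criteria.** Eligibility requires that "participants are medical students in their clinical years (3rd–6th year) at Heidelberg University". On earlier training: "Previous participation in surgical training courses including insertion of chest drains is not an exclusion criterion but will be recorded and analyzed".
- **Randomization.** Blocked, 1:1, stratified by gender only. Allocation uses opaque sealed envelopes, handled by someone outside training, rating and data collection, after recruitment is complete.
- **Assessment.** A pilot showed that the modified OSATS separates experience levels. There is no baseline test on the model, because the curriculum is meant to "prepare novices for their first performance of chest drain placement". The section adds: "To prevent selection bias, baseline characteristics including age, year of studies, previous experience, gender and hobbies will be compared".
- **Secondary endpoints.** Subgroup analyses of operative performance by gender and by experience are planned.
- **Statistical analysis.** The primary outcome is "tested using analysis of covariance with intervention group as factor", with the participants' "self-attributed expertise score as covariate and OSATS score after intervention as dependent variable". No other term is named.

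**The concern.** With no baseline OSATS, the model can gain precision only from other variables known before training. The plan uses one, a subjective self-rating. It leaves out two more objective items that it already collects, chest-drain training and year of studies, and it leaves out the factor used to stratify the randomization. By the article's own account the score responds to experience, so these items may well be prognostic. What is at stake is the width of the confidence interval and the power of a trial sized with almost no margin.

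Two statements in the Assessment section add to the concern. Comparing baseline characteristics is offered as a means of preventing selection bias, which a comparison made after allocation cannot do. The reason for having no baseline test describes novices at their first drain, while the eligibility rule admits students who may have been trained in the procedure.

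**Working it through.** **Inputs.** Difference 3, SD 5 (reading the ± 5 in Sample size determination as the SD), α 0.05 (taken as two-sided; the article does not say), power 0.80, 45 per arm.

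**1. The plan's own figure.** The standardized difference is 3/5 = 0.6. A two-sided t-test needs 44.6, rounded up to 45 per arm (44 by the normal approximation). Power at 45 per arm is 80.4%. A one-sided test would need 35, which does not fit. The stated size is reproduced.

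**2. Gain from added covariates.** If they explain an additional share R² of the outcome variance, the residual SD is 5·√(1 − R²) and the noncentrality is 3 / [5·√(1 − R²)·√(2/45)]. The documents give no R², so the values below are assumptions. They also suppose that the expertise score explains nothing.

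| Assumed additional R² | Residual SD | Power at 45 per arm |
|---|---|---|
| 0 | 5.00 | 80.4% |
| 0.05 | 4.87 | 82.3% |
| 0.10 | 4.74 | 84.3% |
| 0.20 | 4.47 | 88.2% |

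**3. Allowing for the expertise score.** Only variance beyond that score counts. Suppose it already explains 0.20 and the added variables bring the total to 0.25. Power then moves from 88.2% to 90.1%, a gain of about 2 points.

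**4. Cost of the extra terms.** The planned model leaves 90 − 3 = 87 residual degrees of freedom. Gender, training and a linear year term take 3 (84 left). With year as a four-level factor they take 5 (82 left). The change in critical value costs less than 0.1 percentage point of power. Chance correlation between covariates and arm costs more. For k terms not balanced by design, the variance of the group effect rises on average by about 1/(1 − k/89). Gender is nearly balanced by the stratification, so k is 2 with linear year and 4 with the factor. The break-even R² is therefore about 2/89 = 0.02 or 4/89 = 0.045. With this cost included, the three power figures become 81.4%, 83.5% and 87.5% (linear year) or 80.5%, 82.6% and 86.7% (factor).

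**5. Omitting the stratification factor.** Stratified blocks hold gender nearly equal between arms, so gender adds almost nothing to the true variance of the group difference, yet its variance stays in the model's residual. If gender explains a share R² of the residual variance, the reported standard error is too large by about 1/√(1 − R²): 1/√0.95 = 1.026 at an assumed 0.05, and 1/√0.90 = 1.054 at 0.10.

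**6. Chance imbalance in prior training.** The 95% range of the difference between arms is ±1.96·√(2p(1 − p)/45): ±12 percentage points at an assumed prevalence of 10% and ±19 at 30%. The test's error rate already allows for this imbalance. It is not a bias.

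**7. The two statements in Assessment.** Selection bias at allocation is prevented by the procedure in the Randomization section: recruitment completed first, then concealed envelopes. The later comparison only describes the result. The phrase "prepare novices for their first performance of chest drain placement" cannot hold for every participant when earlier chest-drain training is no bar to entry.

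**The case against.** The best defence is that a single covariate fixed in advance is a legitimate choice. Omitting a prognostic variable from a randomized comparison neither biases the estimate nor inflates the type I error. Experience is not ignored either: it is to be recorded and analyzed, it defines planned subgroup analyses, and the expertise score is itself a measure of it. The pilot finding does not say which experience levels the tool separates, so it cannot be turned into a share of variance among 3rd to 6th year students. All of this stands, and it limits the point to precision.

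Several stronger readings are tempting, and the documents do not support them:

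- **Experience is merely compared between arms.** This is untrue for prior experience, for the reasons just given. It fits year of studies only, where comparison is the sole use named. Subgroup analyses, however, ask whether the effect differs by experience; they do not adjust the primary estimate.
- **Participants vary widely in experience.** The eligibility rule permits variation, but no distribution is given.
- **Comparing five characteristics gives a 23% chance of a spurious difference (1 − 0.95⁵).** This needs five independent tests. The article does not say that baseline characteristics will be tested. Gender is balanced by design, and age and year of studies are related.
- **The comparison opens the door to choosing covariates afterwards.** The article fixes its covariate in advance and ties no adjustment to the baseline comparison.

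**Conclusion.** The point holds as one about precision and wording. The stated primary model leaves out prior chest-drain training, year of studies and gender, all of which the trial collects, and relies on one subjective covariate although there is no baseline OSATS. The group comparison remains valid and the sample size of 45 per arm is reproduced.

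The size of the gain is uncertain. From 80.4%, power rises to about 82%, 84% or 88% at an assumed additional R² of 0.05, 0.10 or 0.20 if the expertise score explains nothing, and by about 1 to 1.5 points less once the cost of estimating the extra terms is counted (step 4). It will be smaller still where the expertise score already carries the same information, and close to nil if the added variables explain only a few percent. The case for including gender does not depend on a large effect, because the analysis should reflect the stratified design.

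Two textual faults need no assumption: a baseline comparison cannot prevent selection bias, and the description of participants as novices conflicts with the eligibility rule.

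**What to change.** 1. In Statistical analysis, pre-specify gender, prior chest-drain training (yes/no) and year of studies as covariates in the primary ANCOVA, beside the expertise score, and state that this score is taken before the intervention. State how year enters. One linear term brings the cost to 3 degrees of freedom in all; a four-level factor brings it to 5 and needs more explained variance to pay for itself.
2. In Assessment, report baseline characteristics descriptively by arm and delete the claim that comparing them prevents selection bias. Point instead to concealed allocation after completed recruitment.
3. Reconcile the aim stated for novices with the eligibility rule by giving a supportive estimate in students without prior chest-drain training, within the experience subgroup analysis already planned.

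The changes are to wording and model specification. They need no new data, visits or participants.

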### Randomization

Blocked randomization, stratified by gender, is used to randomly assign participants to each group (1:1 ratio), resulting in one intervention and one control group. Randomization is performed by an employee not involved in training, rating or data collection regarding the present study using opaque, sealed envelopes. As student recruitment to the study will be completed before randomization, any influence of randomization results or subsequent task assignments is considered minimal.

### Training curriculum

Training is conducted according to the structured training curriculum outlined in Fig. 1 (study protocol flow chart) and supervised by experienced surgeons not involved in the randomization or analysis of study results. Students participate in two training sessions lasting 120 min each. At the beginning of the first session and after a theoretic introduction to the procedure, participants in groups 1 and 2 are asked to study the E-learning material assigned to them until they reach an overall app-based score of 100% on performance of the assigned module. Intervention group students use the TS module “Chest Drain Insertion,” while participants in the control group are asked to practice the unrelated module “Central Venous Catheter Insertion.” Control group participants otherwise attend every introduction and assessment included in the training sequence. Performance of the assigned training modules will be monitored to ensure adherence to each group-specific protocol. As this study is conducted in the context of the regular curriculum, dropouts, if any, are expected to be very few. Additionally, we created a highly efficient curriculum. This results in a short intervention period facilitating reduction of attrition bias as suggested by Little et al. [13].

**Fig. 1 Fig1:**
[figure not shown]
Study flow chart

### Assessment

Participants perform chest drain insertion on an accordingly prepared porcine model during the second training session. Performance is videotaped and rated by two different raters on-site using the modified OSATS tool for chest drain insertion (Table 1). The raters are blinded to the training status of the participants. An additional video-based evaluation is performed by a blinded rater according to the same scoring tool. The modified OSATS for chest drain insertion was evaluated in a pilot study and showed good construct validity for distinction between experience levels. Unblinding of raters or employees involved in data analysis and interpretation is not intended. To prevent selection bias, baseline characteristics including age, year of studies, previous experience, gender and hobbies will be compared. Baseline testing on a porcine model is not performed as the hypothesis is that the proposed curriculum, consisting of multimedia training material only, will directly improve performance. The aim of the training curriculum and study is to prepare novices for their first performance of chest drain placement. Baseline testing on a real model could disguise the effect of the training curriculum.

**Table 1 Tab1:** Objective structured assessment of the technical skills score for chest tube insertion

Correct identification of incision location	1 **Poor** The chosen dissection plane deviates tremendously from the suggested site	2	3 **Sufficient** The chosen dissection plane deviates slightly from the suggested site	4	5 **Excellent** 4th/5th intercostal space; mid/anterior axillary line
Correct plane of dissection subcutaneously	1 **Poor** Both distance or execution of tunneling lack accuracy	2	3 **Sufficient** Either distance or execution of tunneling lack accuracy	4	5 **Excellent** Both distance and execution of tunneling are accurate
Blunt dissection on top side of rib	1 **Poor** Flawed dissection; not carried out on top side of rib	2	3 **Sufficient** Solid dissection carried out with minor errors	4	5 **Excellent** Confident cut through the subcutaneous layers and intercostal muscles
Scissors/clamp guarded with other hand during dissection and pulled out without closing the instrument	1 **Poor** Hazardous handling that might affect the patient	2	3 **Sufficient** Improvable handling	4	5 **Excellent** Confident handling of the used instruments
Digital exploration of pleural cavity on chest wall to rule out adhesions	1 **Poor** No digital exploration	2	3 **Sufficient** Finger inserted in pleural cavity	4	5 **Excellent** Digital exploration in 360° with turning of the wrist rules out adhesions
Drain guarded with hand while being inserted	1 **Poor** Hazardous handling that might affect the patient	2	3 **Sufficient** Improvable handling	4	5 **Excellent** Confident handling of the used instruments
Drain inserted into pleural cavity	1 **Poor** Tube advancement is carried out poorly	2	3 **Sufficient** Tube advancement is carried out with minor errors	4	5 **Excellent** Forceps unclamped in time and tube manually advanced.
Estimate made of drain length	1 **Poor** Estimate deviates tremendously from rater’s opinion	2	3 **Sufficient** Estimate deviates slightly from rater’s opinion	4	5 **Excellent** Optimal estimate stated
Economy of time and motion	1 **Poor** Many unnecessary/disorganized movements	2	3 **Sufficient** Organized time/motion, some unnecessary movement	4	5 **Excellent** Maximum economy of movement and efficiency
Amount of help/assistance needed from tutor	1 **Poor** Task could not be carried out without extensive assistance	2	3 **Sufficient** Trainee only raises important questions in order to maximize performance	4	5 **Excellent** Almost no assistance needed; task is carried out confidently

